## Statistical methods

### Statistical methods for primary and secondary outcomes {20a}

Primary analysis will be considered at the 6-month end point using a multi-level logistic regression model to assess the differences between the two treatment groups and will accommodate the within care home-level clustering. Analysis will be conducted on an intention to treat basis, and if required, a per-protocol analysis will be conducted as sensitivity analysis. Stratification variables (site and care home size) will be incorporated into the model. All treatment effect estimates will be presented with 95% confidence intervals. Analysis of secondary outcomes will follow the same analysis model as the primary analysis where possible. Binary outcomes will be analysed using multi-level logistic regression and continuous outcomes with a multi-level mixed effects model. Exploratory analysis will be conducted to establish the effect of cognitive impairment on the outcome.

The independent committees will have the opportunity to comment on this plan. If any deviations from the planned statistical analysis are required, these will be fully documented and justified in the final analysis report.

A nested internal pilot will be conducted across all three geographical areas over 3 months using stop/go criteria, assessing the accumulated data using ACCEPT criteria [55]:Recruitment rate of eligible participants (Green > / = 50% + ; Amber 40–49%; Red <39%);Number who remain engaged with the study and that we expect to follow-up at 6 months (Green > / = 72% + ; Amber 61–71%; Red <60%);Fidelity rate from the participating clinicians (Green > / = 80%; Amber 70–80%; Red <69%);Data completion rate for the POM (Green > / = 80%; Amber 70–80%; Red <69%);Confirmation that cost data is available and that appropriate cost information can be collected from the setting to inform the health economic evaluation;Confirmation of the social acceptability of the intervention for residents, formal carers and care home managers; andNo adverse events (see adverse events below) that are considered by the Data Monitoring Committee to highlight an unacceptable risk to enrolled participants.

In this manner, the internal pilot will test the trial procedures and check that we can recruit and retain participants. Equally, it will ensure that any adaptations made to the study will still be valid for the main analysis.

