### Outcomes {12}

#### Primary outcome in the trial

The Primary Outcome Measure (POM) for this study will be the Silness-Loë Plaque Index [42]. The index is a 4-point scale (measuring the amount of dental plaque present on six index teeth) ranging from 0-no plaque to 3-abundance of dental plaque within the gingival pocket and/or on the tooth and gingival margin. In accordance with the index, the mean will be calculated from these ordinal scores on the six index teeth. The prevailing model in the dental literature is to measure the change in this mean score. However, this model is difficult to infer clinical significance at a population level. To this end, the proportion of individuals in each arm that have demonstrated a 50% reduction in their mean Silness-Loë Plaque Index from baseline will be calculated. This will enable the change in the mean plaque index at the individual level to be measured, whilst providing a meaningful primary outcome measure at a population level.

The sample size calculation (see section ‘Sample size {14}’) is based and powered on changes to the POM at 6 months. This takes account of the ‘time-to-effect’ of the intervention on the POM and the pragmatic consideration of the length of stay of eligible residents. However, a follow-up at 12 months will be undertaken to determine whether the effect seen at 6 months can be sustained. This aligns with the eligibility criteria and the estimated length of stay that the residents have in a care home [43].

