#### Secondary outcomes

Clinical outcomes (assessed at baseline, 6 months and 12 months) will include the number of new carious lesions (coronal and root caries) and episodes of bleeding on probing. This will be undertaken on the same index teeth (according to Ramfjord) to reduce the burden on participating residents [44];Health−related quality of life (HRQoL) will be assessed at baseline, 6 months and 12 months using the EuroQol five dimensions questionnaire (EQ−5D5L) [45]. The EQ−5D5L is an established HRQoL outcome and is also relevant for a cost−utility analysis;Oral health−related quality of life (OHRQoL) will be assessed at baseline, 6 months and 12 months using the Oral Impacts on Daily Performances (OIDP) [46]. This will assess the impacts of oral conditions on daily life. It is a widely used OHRQoL outcome also applied in care homes in the UK;Oral symptoms, episodes of pain and episodes of unscheduled care; andThe number of onward referrals to dentists, when the treatment needed extends beyond the DTs’ Scope of Practice [33].

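### No analysis of the mean plaque index is listed beside the halved-or-not primary endpoint, and baseline plaque is not among the named covariates

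*Protocol article*

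**What the plan says.** All references are to the protocol article.

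- **Measure collected** (Primary outcome in the trial): "In accordance with the index, the mean will be calculated from these ordinal scores on the six index teeth". Each resident therefore has a near-continuous score between 0 and 3 at baseline, 6 and 12 months.
- **Primary endpoint** (same section): "the proportion of individuals in each arm that have demonstrated a 50% reduction in their mean Silness-Loë Plaque Index from baseline will be calculated".
- **Reason given** (same section): the protocol acknowledges that "The prevailing model in the dental literature is to measure the change in this mean score", then objects: "However, this model is difficult to infer clinical significance at a population level".
- **Primary model** (Statistical methods for primary and secondary outcomes {20a}): the 6-month comparison is made "using a multi-level logistic regression model to assess the differences between the two treatment groups", with clustering by home. On covariates: "Stratification variables (site and care home size) will be incorporated into the model".
- **Secondary outcomes**: the clinical ones "will include the number of new carious lesions (coronal and root caries) and episodes of bleeding on probing". The rest are EQ-5D-5L, OIDP, symptoms with pain and unscheduled care, and onward referrals. The mean plaque index is not listed.
- **Model for other outcomes** ({20a}): "Binary outcomes will be analysed using multi-level logistic regression and continuous outcomes with a multi-level mixed effects model". This is general and assigns no model to plaque.
- **Additional analyses {20b} and missing data {20c}**: these name a cognition sensitivity analysis, a per-protocol analysis, multiple imputation, predictors of missingness as possible model terms, and sensitivity analyses of modelling and missing-data assumptions. None is an analysis of mean plaque.

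**The concern.** The aim and the first objective are to reduce plaque levels, yet the only plaque analysis listed counts residents who cross one threshold. A resident whose score falls by 45% counts the same as one whose score does not change. A moderate and real fall across the intervention homes could leave the primary result inconclusive, with no pre-specified estimate of its size to fall back on.

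The protocol's own planning evidence shows that this can matter. Of the two studies cited under Sample size {14}, one reports a mean fall from 2.36 to 1.58, which is (2.36 − 1.58)/2.36 = 33%. An average benefit of that size falls short of the halving cut.

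Baseline plaque is an obvious covariate for a continuous analysis, and it enters the present plan only through the definition of the response.

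**Working it through.** **Inputs from Sample size {14}.** Proportions 0.10 and 0.29 (difference 0.19), 20 homes per arm, 5 completers per home, ICC 0.05, 28% attrition, 5% significance (two-sided assumed), 90% power.

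**1. The plan's own figure.**
- Design effect = 1 + (5 − 1) × 0.05 = 1.20, so the effective n per arm = 100/1.20 = 83.3.
- Variance (unpooled) = 0.10 × 0.90 + 0.29 × 0.71 = 0.2959.
- SE = √(0.2959/83.3) = 0.0596; 0.19/0.0596 = 3.19; power = Φ(3.19 − 1.96) = **89.0%**. The arcsine formula also gives 89.0%, the pooled formula 87.9%.
- Required n per arm before clustering = (1.960 + 1.282)² × 0.2959/0.19² = 86.1. In total, 86.1 × 1.2 × 2/0.72 = 287, against the stated 280.

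The stated design is reproduced to within rounding and choice of formula.

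**2. The same effect on the continuous scale.** Assumption: the underlying change is normal with equal SD in both arms, the intervention shifts it uniformly, and the ICC is also 0.05. The protocol gives no SD.
- Shift d = z(0.29) − z(0.10) = −0.553 + 1.282 = **0.728 SD**.
- n per arm before clustering = 2 × (1.960 + 1.282)²/0.728² = 39.6, so 40. Against 86 to 90 for the binary endpoint (unpooled to pooled), the ratio is 0.44 to 0.46.
- Power with 83.3 effective per arm: 0.728/√(2/83.3) = 4.70; Φ(4.70 − 1.96) = **99.7%**.

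**3. Information kept by a cut at proportion p** = φ(z_p)²/[p(1 − p)].

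| p | Kept | Lost |
|---|---|---|
| 0.10 | 34% | 66% |
| 0.195 (average of the arms) | 48% | 52% |
| 0.29 | 57% | 43% |

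**4. A smaller true effect: 70% of the planned shift.**
- Intervention proportion = Φ(−1.282 + 0.7 × 0.728) = 0.220.
- Binary: 0.120/√[(0.09 + 0.220 × 0.780)/83.3] = 2.14; power = Φ(2.14 − 1.96) = **57%** (56% pooled).
- Continuous: 0.7 × 4.70 = 3.29; power = Φ(3.29 − 1.96) = **91%**.

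**5. Simulation check.** 40 homes of 5 completers, ICC 0.05, assumed baseline mean 1.8, SD 0.5, baseline-to-follow-up correlation r, 2000 trials per setting, calibrated to about 0.10 v 0.29:

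| Analysis | r = 0.3 | r = 0.5 |
|---|---|---|
| Responder | 0.917 | 0.896 |
| Responder with baseline term | 0.916 | 0.894 |
| Continuous, baseline-adjusted | 0.997 | 0.997 |

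A second simulation, with a log-normal change ratio, gave about 0.91 for the responder analysis and above 0.99 for the baseline-adjusted continuous one.

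**6. What a baseline term does for the responder model.** Response means that (6-month score − 0.5 × baseline) is at or below 0. With equal SDs at both visits, the slope of that quantity on baseline is r − 0.5. Using the assumed mean and SD of step 5:
- r = 0.5: the slope is zero, so the chance of response does not depend on baseline, and imbalance moves nothing.
- r = 0.3: an arm with a baseline 0.5 SD higher gains about 1.9 points at 10% and 3.6 points at 29%. A chance imbalance of one standard error, √(2 × 1.2/100) = 0.155 SD, moves them 0.6 and 1.1 points.
- r = 0.7: the direction reverses; a 0.5 SD higher baseline takes 10% to about 8%.

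The planned difference is 19 points.

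**The case against.** The best defence has three parts.

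**The binary endpoint is a reasoned choice.** The protocol explains that a change in mean score is hard to interpret clinically, and it powers the trial for the responder rule. This stands. A reader might infer that the primary analysis is invalid or should be replaced; the document supports neither. The loss is one of efficiency.

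**Covariates and supportive analyses belong to the SAP.** The SAP is not shown, the covariate sentence does not say that nothing else will be included, and {20c} promises sensitivity analyses of modelling assumptions. This stands in part: the SAP may add a baseline term or a continuous analysis. But the protocol itself fixes the list of secondary outcomes, and mean plaque is not on it. If it first appeared in the SAP, it would be an outcome outside the published list.

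**The harm from omitting baseline plaque is easily overstated.** This stands. Because residents are enrolled after homes are allocated, a reader might infer that baseline imbalance is likely and goes uncorrected, and that adjustment would remove the resulting bias. The document gives no basis for calling imbalance likely. Its effect on the responder endpoint is nil at r = 0.5 and a few points at r = 0.3, and no covariate corrects for unmeasured differences between those enrolled.

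A reader might also infer that the results could not be set beside the two planning studies. That does not follow: the mean is to be calculated for every resident, so arm means can be reported. What is absent is a pre-specified comparison of them.

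**Conclusion.** The concern holds as a gap in the listed analyses. The trial collects a near-continuous plaque score on every resident but lists no analysis of it, and the covariates named for the primary model omit its baseline value. Under a uniform normal shift with equal SDs and an ICC of 0.05, the cut costs about half of the information. A continuous analysis would have much the better chance of detecting an effect smaller than planned.

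These figures depend on the assumed shift. The protocol gives neither the SD of plaque nor its correlation over time, and the continuous advantage could differ if the intervention helps only a subset of residents.

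The baseline term matters mainly for the continuous model. In the primary logistic model it adds little or no power. There it reduces, but does not remove, any bias from imbalance in measured baseline plaque, and the benefit depends on the unknown correlation.

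This is a worthwhile improvement to make, not an error that undermines the primary result.

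**What to change.** 1. Keep the responder endpoint as primary.
2. Under Secondary outcomes, add the 6-month mean plaque index as the first secondary outcome. In {20a}, specify a linear mixed model with a home random effect, site, home size and baseline mean plaque index, reporting the adjusted mean difference with its 95% confidence interval.
3. Optionally, add baseline mean plaque index as a continuous covariate in the primary logistic model, stated before any outcome data are seen.

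The cost is protocol and SAP wording and one extra model on data already collected. The article describes the trial as pre-recruitment, so at that stage the change could be made without any suspicion that it was driven by data.

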**Fig. 2 Fig2:**
[figure not shown]
Time schedule of enrolment, interventions, assessments and visits for participants

The care homes allocated to the intervention arm will be asked to implement the oral health intervention during the study period (12 months, *t*_0_ to *t*_2_), and the care homes allocated to the control arm will be asked to continue with routine practice during the same 12-month period. Assessments (intervention and control group) will be undertaken at baseline (*t*_0_), 6 months after baseline (*t*_1_) and 12 months after baseline (*t*_2_).

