### Sample size {14}

The primary outcome will be based on a binary outcome using a superiority design, with a successful case demonstrating a 50% reduction in their mean Silness-Löe Plaque Index [42] over a 6-month period, i.e. the relative proportion of the residents whose Silness-Löe Plaque Index have been halved as a result of the intervention will be compared across the two arms. This concurs with two relevant studies, which tested the implementation of an oral hygiene guideline in a comparable population. Khanagar et al. [47] demonstrated a 50% reduction in the mean Silness-Löe Plaque Index (3.17 to 1.57), and the mean reduction amongst residents found by van der Putten et al. [48] was from 2.36 to 1.58. Assuming the proportion of the control group that will halve their mean Silness-Löe Plaque Index over 6 months is 0.10 (given the halo effect of participating in a trial), a sample of 280 (20 care homes per arm with five completers per care home plus attrition at 28%) will provide 90% power to detect a 0.19 difference in proportions between the arms at a 5% significance level (i.e. 0.29 of intervention group will see a 50% reduction in their mean Silness-Löe Plaque Index). This incorporates an intraclass correlation coefficient of 0.05. The measurements taken at 12 months will determine whether this effect (the primary end point being 6 months) can be sustained for a further 6 months.

It is likely that care homes will be able to recruit a variable number of participants due to their relative size and differing populations. Therefore, a coefficient of variation has been included in the sample size to accommodate this. Taking the approach of Campbell and Walters [49] and assuming that recruitment will vary between 5 and 15 participants within a home the sample proposed will accommodate this and still retain 90% power.

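### The pilot's plaque-completion criterion cannot check the 6-month primary outcome and is not reconciled with the 28% attrition allowance; the colour bands overlap and leave gaps

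*Protocol article*

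**What the plan says.** The internal pilot is described in the protocol article under Statistical methods for primary and secondary outcomes {20a}: "A nested internal pilot will be conducted across all three geographical areas over 3 months using stop/go criteria". Two of its criteria bear on how many residents can be analysed.

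- Retention: "Number who remain engaged with the study and that we expect to follow-up at 6 months", green from 72%, amber 61-71%, red below 60%.
- Completion of the primary outcome measure (POM), the Silness-Löe Plaque Index: "Data completion rate for the POM (Green > / = 80%; Amber 70–80%; Red <69" per cent. No time point or denominator is given.

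Recruitment is green from 50%, amber 40-49%, red below 39%. Fidelity has the same limits as POM completion.

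Under Outcomes {12}, success is a halving of the resident's mean plaque index from baseline, judged at 6 months, so each resident needs two scores. Participant timeline {13} places the assessments at baseline, "6 months after baseline" and at 12 months. Sample size {14} rests on "20 care homes per arm with five completers per care home plus attrition at 28" per cent, and states that this "will provide 90% power to detect a 0.19 difference in proportions between the arms".

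**The concern.** A stop/go rule has to be computable from the data available when it is applied, and its green level should be compatible with the sample size. The POM completion criterion falls short on both counts. Three months into the trial nobody has a 6-month plaque score, so the criterion says nothing about whether the primary outcome will be obtained. In addition, retention at its green minimum already spends the whole attrition allowance, yet POM completion is still green with a fifth of scores missing.

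Some whole-number results also fall in two colours or in none, so the rule gives no clear answer for them.

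At stake is a green rating for a trial that may fall short of its planned completers. This matters because Interim analyses {21b} plans no interim analysis, and the pilot is the only stop/go check on retention and data completion that the article describes.

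**Working it through.** **Inputs.** From Sample size {14}: 280 recruited; 20 homes per arm; 5 completers per home (200 in all); attrition 28%; proportions 0.10 and 0.29; ICC 0.05; 5% significance; 90% power. From the pilot criteria in {20a}: green minima of 72% (retention) and 80% (POM completion). Assumed: a two-sided test, and equal home sizes because the coefficient of variation is not given.

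**Timing.** The pilot lasts 3 months and plaque is scored at 0, 6 and 12 months. On the reading that the decision falls at the end of those 3 months, the only plaque data in hand are baseline scores.

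**The plan's own figures.**
- Attrition: 280 x (1 - 0.28) = 201.6, which matches 200 completers.
- Design effect at 5 per home: 1 + (5 - 1) x 0.05 = 1.20. Effective n per arm: 100 / 1.20 = 83.3.
- Variance sum: 0.10 x 0.90 + 0.29 x 0.71 = 0.2959.
- Power (unpooled normal approximation): 0.19 / sqrt(0.2959 / 83.3) = 3.19; 3.19 - 1.96 = 1.23; power 0.890. The stated 90% is reproduced to within about one point. The pooled version gives 0.879.

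**Both criteria at their green minima.** The number with both scores depends on how the two losses combine, which the article does not say.

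| How the losses combine | Share with both scores | Residents of 280 |
|---|---|---|
| Missing scores fall entirely among residents lost anyway, or drop-outs already count as non-completers (72% binds) | 0.72 | 201.6 |
| Completion counted among retained residents, or independent of retention | 0.72 x 0.80 = 0.576 | 161.3 |
| Losses never overlap | 0.72 + 0.80 - 1 = 0.52 | 145.6 |

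**Power at 161.** Per home: 161.3 / 40 = 4.03. Design effect: 1 + 3.03 x 0.05 = 1.15. Effective n per arm: 80.6 / 1.15 = 70.0. Then 0.19 / sqrt(0.2959 / 70.0) = 2.92; 2.92 - 1.96 = 0.96; power 0.832 (pooled 0.817).

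**Power at the ends of the range.** At 201.6 it is 0.892. At 145.6: 3.64 per home; design effect 1.132; effective n 72.8 / 1.132 = 64.3; 0.19 / sqrt(0.2959 / 64.3) = 2.80; power about 0.80.

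**Sensitivity to unequal homes.** With a coefficient of variation of 0.3 or 0.5, unpooled power is 0.885 or 0.875 at 200 residents, and 0.826 or 0.816 at 161. The loss stays at about 6 points.

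**Bands, read in whole percentages.**

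| Criterion | Green | Amber | Red | Fault |
|---|---|---|---|---|
| Recruitment | 50 or more | 40-49 | below 39 | 39 has no colour |
| Retention | 72 or more | 61-71 | below 60 | 60 has no colour |
| Fidelity | 80 or more | 70-80 | below 69 | 80 in two bands; 69 has no colour |
| POM completion | 80 or more | 70-80 | below 69 | 80 in two bands; 69 has no colour |

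Rounding to whole numbers does not remove these faults.

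**The case against.** **The retention criterion looks forward.** A reader might infer that it claims to observe 6-month follow-up. From there the reader might argue that 72% still present at month 3 means 0.72 x 0.72 = 52% at month 6, or about 145 residents. The text does not support this. The criterion counts residents whom the team expects to follow up at 6 months, so it is a projection, and comparing it with 72% is coherent. A pilot already down to 72% and expecting further loss would not be green as worded. Squaring also needs a constant-loss assumption that the article does not make. This objection stands in full. The lower limit of 146 above has a different source: non-overlapping losses at the two stated thresholds.

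**The figure of 161 depends on the denominator.** If POM completion is counted over all recruited residents, with drop-outs as non-completers, there is no shortfall. This stands as a reason to give a range. It does not rescue the criterion. That count needs 6-month data, which the pilot will not have. It would also prevent a trial exactly on plan, at 72% retention, from ever reaching 80%.

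**Green minima are the worst green case, and amber is not a go.** Both are true. The Trial Steering Committee decides on continuation, and a green pilot may do better than its minima. The point concerns what the rule permits.

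**Multiple imputation is planned where appropriate ({20c}).** It would keep residents in the analysis but would not fully restore the missing information.

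**The band edges are editorial.** They will seldom decide the outcome, but they are decision limits and cost nothing to correct.

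**Conclusion.** The concern holds, limited to two faults in the stop/go rule.

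1. The POM completion criterion lacks a time point and denominator, can only be baseline completion in a 3-month pilot, and is not reconciled with the 28% allowance. At both green minima the trial could have about 161 residents with paired scores if the rates multiply (range about 146 to 202), against 200 planned. Power at 161 is about 82-83%; the same methods give 88-89% at 200. This rests on a two-sided 5% test, the plan's proportions and ICC, and equal home sizes.
2. The bands overlap at 80% for fidelity and POM completion, and assign no colour to 39%, 60% and 69%.

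It does not follow that any green pilot leads to 161 residents, or that the primary question becomes unanswerable. Running a pilot that reports before the primary time point is a legitimate choice. The fault lies in what this one criterion can measure then and how its threshold was set.

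**What to change.** - State that POM completion at the pilot decision means completion of the baseline plaque score, and name the denominator.
- Judge go/no-go on the expected share of recruited residents with both a baseline and a 6-month plaque score, combining projected 6-month follow-up with POM completion. Set green at about 72% (200 / 280 = 71.4%). For example, 80% follow-up with 90% completion meets it if the rates multiply (0.80 x 0.90 = 0.72).
- State the assumption used to project follow-up to month 6. No particular form is required.
- Recompute the share from actual paired scores when the pilot homes reach month 6.
- Close the bands: for fidelity and POM completion, green 80 or more, amber 70 to below 80, red below 70. For recruitment, amber 40 to below 50 and red below 40. For retention, amber 61 to below 72 and red below 61.

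The cost is a rewording of the criteria and one later check on data that will be collected anyway. The article describes the trial as not yet recruiting. The drawback is that the pilot becomes somewhat harder to pass.

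### The internal pilot's stop/go bands overlap at 80% and leave 39%, 60% and 69% in no band

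*Protocol article*

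**What the plan says.** Statistical methods {20a} describes the pilot as follows: "A nested internal pilot will be conducted across all three geographical areas over 3 months using stop/go criteria". Four of its criteria are numeric:

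- Recruitment: "Recruitment rate of eligible participants (Green > / = 50% + ; Amber 40–49%; Red <39" per cent.
- Retention, meaning those expected to be followed up at 6 months: "follow-up at 6 months (Green > / = 72% + ; Amber 61–71%; Red <60" per cent.
- Fidelity: "Fidelity rate from the participating clinicians (Green > / = 80%; Amber 70–80%; Red <69" per cent.
- POM completion: "Data completion rate for the POM (Green > / = 80%; Amber 70–80%; Red <69" per cent.

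The other three criteria (cost data, social acceptability, adverse events) carry no figures. The article states no rounding convention and no tie rule, and nothing elsewhere in it assigns the boundary values. Interim analyses {21b} says that no interim analysis is planned and that there are no formal stopping guidelines.

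**The concern.** A progression rule is fixed in advance so that the data, and not the reader, determine the colour. That requires each possible result to fall in exactly one band. Here the red band stops a full percentage point below the start of amber in every criterion. In two criteria the amber band also runs up to and includes the value at which green starts. With no interim analysis, these bands are the only numeric continuation rule in the article. At the edge between stopping and continuing, the rule returns no colour, so someone has to choose one after seeing the result. This is not detail left to the SAP: the thresholds are printed in full, and they are inconsistent as printed.

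**Working it through.** **Inputs.** The bands are those printed in Statistical methods {20a}. The planning figures come from Trial design {8} and Sample size {14}.

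**Step 1: band membership.** For a percentage p, count the bands that contain it: (p ≥ lower green limit) + (lower amber ≤ p ≤ upper amber) + (p < red limit). A usable rule gives 1 for every p. A count of 0 is a gap and 2 is an overlap.

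| Criterion | Whole per cents in no band | Whole per cents in two bands | Gaps if unrounded |
|---|---|---|---|
| Recruitment | 39 | none | 39 to <40; >49 to <50 |
| Retention | 60 | none | 60 to <61; >71 to <72 |
| Fidelity | 69 | 80 | 69 to <70 |
| POM completion | 69 | 80 | 69 to <70 |

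Rounding to whole per cents would close the 49–50 and 71–72 gaps. It cannot resolve 39, 60, 69 or 80, which are already whole numbers.

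**Step 2: such values can occur.** 24/30 = 80.0% is green and amber. 18/30 = 60.0% has no band. 25/35 = 71.4% retention has no band unless rounded. The last is also the design's own ratio: five completers from an average of seven recruits per home, 5/7 = 200/280 = 71.4%. A pilot that retained residents in exactly that ratio would have no colour if unrounded, and would be amber if rounded to 71%.

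**Step 3: how often.** The article gives no pilot size, so the sizes here are assumptions, and residents are treated as independent. With X ~ Binomial(n, p):

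- n = 70, p = 0.80: P(X = 56) = 0.118, an observed 80%, green and amber.
- n = 70, p = 0.60: P(X = 42) = 0.097, an observed 60%, no band.
- n = 100, true rate equal to the gap value: P(X = 39) = 0.082, P(X = 60) = 0.081, P(X = 69) = 0.086.
- n = 140: the lowest value is 0.067, for 69/140 = 49.3% with a true recruitment rate of 49.5%. The highest is 0.137, for retention of 84/140 or 85/140 (60.0% or 60.7%) with a true rate of 60% to 60.5%.

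**Step 4: limits of these figures.** They apply when the true rate is near a boundary. With n = 70, P(X = 42) falls to 0.020 if true retention is 70%, and to 0.009 if it is 72% (the planned 28% attrition). Some gaps cannot be reached at some sizes: no count out of 70 falls in 39 to <40% or 69 to <70%, and no count out of 100 falls strictly between 49% and 50% or between 71% and 72%.

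**Step 5: the bands after repair.** With green ≥ g, amber ≥ r and < g, and red < r, every percentage has a count of exactly 1.

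**The case against.** The strongest reply is that little turns on this. The article attaches no automatic action to any colour. Composition of the coordinating centre and trial steering committee {5d} gives the steering committee responsibility for continuing or terminating the trial, and that committee would weigh seven criteria, three of them non-numeric. An edge value leaves one label unclear but does not leave the trial without a decision. The 80% overlap lies between green and amber, not at the stopping edge. The decimal gaps vanish if whole per cents are intended. The probabilities place the true rate at or near the boundary, use assumed sizes, and ignore that fidelity and recruitment have denominators other than recruited residents. The slip looks like a less-than sign typed where less-than-or-equal was meant, and calling 39, 60 and 69 red makes a choice that belongs to the trial team.

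Most of this limits the impact, and it is fair. It does not remove the error. A committee with final authority still needs criteria that classify each result once, and one unassigned whole number per criterion survives any rounding. If the sign was mistyped, then 39, 60 and 69 are red, which agrees with the repair proposed here. If the team meant them as amber, it need only say so.

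**Conclusion.** The point holds. All four numeric pilot criteria are misstated: one whole percentage has no band in each (39, 60, 69 and 69), and 80% has two in fidelity and POM completion. This follows from the printed text and needs no assumption. How often it would matter does rest on assumptions. With 70 to 140 pilot residents and a true rate at or near an attainable gap or overlap, the chance of an unclassified or doubly classified result is about 7% to 14% per criterion, and it is much lower elsewhere. The primary endpoint, sample size, type I error and primary analysis are not affected. The correction should be made because the defect is in a decision rule and costs almost nothing to remove, not because it threatens the trial's main result.

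**What to change.** Restate the four criteria on shared cut-points, taken from the article's own lower green and lower amber limits:

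- Recruitment: green ≥50%; amber ≥40% to <50%; red <40%.
- Retention: green ≥72%; amber ≥61% to <72%; red <61%.
- Fidelity: green ≥80%; amber ≥70% to <80%; red <70%.
- POM completion: green ≥80%; amber ≥70% to <80%; red <70%.

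Apply the bands to the unrounded percentage. The cost is four lines of wording before the pilot opens; Trial status places the trial in the pre-recruitment phase. The downside is that values such as 39%, 60% and 69% become red, slightly stricter than the printed red limits. If the team intended them as amber, it should lower the amber limits to 39, 60 and 69 and set red strictly below them, which also closes the gaps.
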